#### Physical activity

Patients complete the Godin Leisure-Time Physical Activity Questionnaire [44,45], which has been modified to include the average duration of activities at baseline and three, six, and 12-months post-enrollment. This questionnaire will be used to estimate weekly minutes of moderate and vigorous activity physical activity, with time spent in moderate physical activity being the primary outcome. Weekly minutes of vigorous activity and average weekly frequency of mild, moderate, and strenuous intensity exercise will also be examined to evaluate change in physical activity behaviors. Additionally, at baseline and 12-months post-enrollment, participants will complete the Nurse’s Health Study Physical Activity Question Index [46], which asks about the average time a person spent doing specific recreational activities in a typical week during the past year.

#### Socio-demographics characteristics

As part of the baseline survey, participants complete items in the Sociocultural Module of the United States Department of Health and Human Services Breast Cancer Core Questionnaire to assess age, ethnicity, education level, marital status, employment status, and income [47,48]. A participant’s perceived financial status of her household also was assessed, as was presence of Ashkenazi ancestry.

#### Intervention engagement

At three months post-enrollment, participants report the time they spent with the intervention materials, their engagement with the materials, their attention to the intervention messages, and the salience of the messages for them [49]. Salience will be measured by rating participants’ degree of interest in the intervention messages and how personally relevant the messages were. While the booklet is the primary intervention component, we will collect aggregate data on website usage. These data will provide valuable insight into the use of intervention components that will inform future interventions and research.

### Planned analyses

For the primary outcome, attention to fertility, the YWI and PAI will be compared in terms of attention to fertility issues as reported in the medical records using general estimating equations (GEE) to evaluate binomial proportions with clustered binary data [50]. GEEs will include terms for treatment arm and stratum, and population-averaged contrasts will be used to test the effects of the YWI versus PAI on attention to fertility. Generalized linear mixed models (GLMMs) will be used in subsequent analyses to describe the effect of the YWI with practice incorporated as a random effect, accounting for covariates such as patient demographics and, if appropriate, including variables in the secondary analyses as well as practice-level characteristics such as setting (urban, suburban, rural) and size of practice. Similar analyses will be conducted using attention to fertility as reported by patients. All analyses will be based on the intent-to-treat (ITT) population, consisting of all subjects at all randomized sites.

For the secondary analyses, examining the effect of the YWI on patients’ emotional health, distress, and quality of life, we will estimate proportions within each arm for each measure and report 95% confidence intervals. Lastly, to examine the effects of the PAI on improvement and maintenance of exercise behaviors, we will determine the mean change in exercise time at three months (post – pre) using a 2-sample t-test adjusting for within-practice correlation for both the PAI and YWI. We will examine change in exercise behaviors at six and twelve months to evaluate maintenance.

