**Methods/Design:**

The study employs a cluster randomized design including 14 academic institutions and 40 community sites across the U.S. assigned to either the study intervention arm or contact-time comparison intervention arm. Academic institutions enroll up to 15 patients per site while community sites enroll up to 10 patients. Patient eligibility requirements include: an initial diagnosis of stage I-III invasive breast cancer within three months prior, without a known recurrence or metastatic breast cancer; 18–45 years of age at diagnosis; ability to read and write in English. The primary outcome is oncologists’ attention to fertility concerns as determined by medical record review. Secondary outcomes include differences in patient satisfaction with care and psychosocial distress between the two study arms.

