Based on our prior experience with designing a unique in-clinic program for young women with breast cancer [25,26], we developed Young & Strong, a print-based educational and supportive care intervention with a corresponding website for young women (18–45 years of age) newly diagnosed breast cancer and their providers. The intervention addresses issues salient to this population (e.g., body image, child care, fertility, education, and career issues). We hypothesize that an intervention that simultaneously increases providers’ awareness of salient issues and educates and encourages patients to communicate with their doctors about these important topics has the potential to reduce psychosocial distress and improve satisfaction with care among young breast cancer patients. Therefore, the primary aim of the Young & Strong study is to evaluate the effect of the Young Women’s Intervention (YWI) on oncologists’ attention to fertility issues compared to a contact-time comparison intervention focusing on physical activity (PAI). Secondary aims include exploring how YWI affects attention to other issues important to young women with breast cancer, including genetic testing, satisfaction with care, distress, and quality of life.

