**Table 1 Tab1:** **Measures and time of assessment in the young & strong study**

**Measure**	**Assessed by**	**Time of assessment**
Attention to fertility		
	• Medical Record Review	3- and 6-mo
	• Fertility Issues Survey [35]	3-, 6- and 12-mo
Anxiety, depression, and distress		
	• Hospital Anxiety and Depression Scale (HADS) [37]	BL, 3- and 12-mo
	• Center for Epidemiologic Studies Depression Scale (CES-D) [39]	BL, 3- and 12-mo
	• Perceived Stress Scale (PSS) [40]	BL, 3- and 12-mo
Health-related quality of life		
	• Cancer Rehabilitation Evaluation System-SF (CARES-SF) [41,42]	3- and 12-mo
Contraception		
	• Items used in prior work assessing methods of contraceptive use among young women with breast cancer at diagnosis and over time [36].	3- and 12-mo
Satisfaction with care		
	• Short-Form Patient Satisfaction Questionnaire (PSQ-18) [43]	3-mo
Physical activity		
	• Godin Leisure Time Physical Activity Questionnaire [44,45]	BL, 3-, 6- and 12-mo
	• Nurse’s Health Study Physical Activity Question Index [46]	BL, 12-mo
Intervention engagement		
	• Items used in prior work to gauge use of intervention materials [49]	3-mo
Socio-demographics		
	• United States Department of Health and Human Services Breast Cancer Core Questionnaire to assess age ethnicity, education, marital status, employment status [47,48]	BL
	• Participants’ perceived financial status of their household	
	• Ashkenazi ancestry	

Note: BL = baseline.

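### The follow-on mixed model for the YWI effect may adjust for secondary outcomes measured after the intervention, which can bias the adjusted effect; the primary GEE test is not affected

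*Protocol article*

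**What the plan says.** All of the following is in the protocol article.

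- **Primary test of attention to fertility** (Planned analyses): "GEEs will include terms for treatment arm and stratum, and population-averaged contrasts will be used to test the effects of the YWI versus PAI". No other covariate enters.
- **Follow-on model** (Planned analyses): "Generalized linear mixed models (GLMMs) will be used in subsequent analyses to describe the effect of the YWI with practice incorporated as a random effect". Similar analyses are planned for attention to fertility as reported by patients.
- **What the follow-on model may adjust for** (Planned analyses): "accounting for covariates such as patient demographics and, if appropriate, including variables in the secondary analyses as well as practice-level characteristics". Practice setting and size are the examples of the last group.
- **What the secondary variables are**: the next paragraph begins "For the secondary analyses, examining the effect of the YWI on patients’ emotional health, distress, and quality of life". The Abstract adds satisfaction: "Secondary outcomes include differences in patient satisfaction with care and psychosocial distress between the two study arms".
- **When they are measured** (Table 1): PSQ-18 at 3 months only; CARES-SF at 3 and 12 months; HADS, CES-D and PSS at baseline, 3 and 12 months.
- **Population** (Planned analyses): "All analyses will be based on the intent-to-treat (ITT) population, consisting of all subjects at all randomized sites".

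**The concern.** A covariate-adjusted treatment effect keeps the protection of randomisation when its covariates cannot have been changed by treatment. Here the permitted list includes variables that the plan itself analyses as effects of YWI. The Background hypothesises that the combined intervention "has the potential to reduce psychosocial distress and improve satisfaction with care among young breast cancer patients", and it also expects attention to these issues to raise satisfaction and so lower distress. A follow-up score may therefore be a consequence of both the arm and the outcome being modelled.

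What is at stake is how the adjusted estimate can be read. With such a score in the model, the arm coefficient compares women who ended up with the same satisfaction or distress, which is not the effect of assigning a site to YWI. A second, conditional consequence is that a woman with a known chart outcome but no survey could drop out of the model.

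**Working it through.** The plan gives no figure for this model, so there is none to reproduce. The check has three parts.

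**1. Can the clause be read as baseline only?**

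| Secondary variable | Baseline value (Table 1)? | Can be entered as pre-intervention? |
|---|---|---|
| HADS, CES-D, PSS | yes | yes; the baseline survey precedes the patient's materials |
| CARES-SF | no (3 and 12 months) | no |
| PSQ-18 | no (3 months) | no |

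A baseline-only reading works for distress. It cannot work for quality of life or satisfaction.

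**2. When does adjustment for a follow-up score bias the arm effect?**

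Inputs from Statistical design: a PAI rate of 10% and a detectable difference of 28 points, hence 10% v 38%. The effects *b* and *c* below are assumptions; the document gives none.

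Let *Y* be attention to fertility, *A* the arm, and *S* = *bY* + *cA* + N(0,1) the follow-up score in SD units. By Bayes' rule,

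logit P(Y=1 | A, S) = logit P(Y=1 | A) + bS − b²/2 − bcA.

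The arm log odds ratio therefore shifts by exactly −*bc*, and the odds ratio is multiplied by exp(−*bc*). The unadjusted odds ratio is (0.38/0.62)/(0.10/0.90) = 5.52.

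| b (attention to score) | c (arm to score, direct) | exp(−bc) | Adjusted OR |
|---|---|---|---|
| any | 0 | 1 | 5.52 |
| 0.3 | 0.2 | 0.942 | 5.19 |
| 0.5 | 0.3 | 0.861 | 4.75 |
| 0.8 | 0.5 | 0.670 | 3.70 |
| 0.5 | −0.3 | 1.162 | 6.41 |

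A simulation of 400,000 subjects gave 5.17, 4.73, 3.69 and 6.43 for the four rows with *c* ≠ 0, in agreement.

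That model ignores clustering, whereas the planned model has a practice random effect. A random-intercept logistic model was therefore fitted to one large simulated population: 1,620 practices of 15 or 5 patients, 12,300 patients, marginal rates set at 10% and 38%, and an assumed random-intercept SD of 1.5. The unadjusted log odds ratio was 2.36 (OR 10.6, practice-specific and so not comparable with 5.5).

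| b | c | Adjusted log OR | Retained |
|---|---|---|---|
| 0.2, 0.5 or 0.8 | 0 | 2.35 to 2.36 | 100% |
| 0.2 | 0.2 | 2.31 | 98% |
| 0.5 | 0.5 | 2.06 (OR 7.8) | 87% |
| 0.8 | 0.5 | 1.88 (OR 6.6) | 80% |

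A covariate independent of arm and outcome, standing in for a pre-intervention one, left it at 2.36. Only *b*, *c* ≥ 0 were tried here, so these runs show attenuation and say nothing about inflation.

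Is a direct arm effect (*c* ≠ 0) plausible? Yes. Under Overview of the interventions, the YWI materials cover coping with anxiety, body image and sexual functioning, and these can act on the scores without any fertility note in the chart.

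**3. Who is left in the model?**

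The primary outcome comes from medical record review and needs no survey. If the GLMM is fitted to complete cases, entering a 3-month score removes survey non-responders. Response rates are not given. At an assumed 90, 80 or 70%, 369, 328 or 287 of the minimum 410 patients remain (410 × 0.9, 0.8, 0.7).

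In the same simulated population, response unrelated to *Y*, or related to it equally in both arms, left the log odds ratio at 2.36 to 2.37. Response related to *Y* differently by arm moved it:

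- to 2.64 with 75% response throughout except 95% among YWI women with attention documented;
- to 2.03 with 80% response in PAI, and in YWI 90% without and 70% with attention documented.

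**The case against.** The strongest reply is that this is an optional, descriptive model. The confirmatory comparison is the GEE with arm and stratum only. The clause is conditional, the distress scales have baseline values that may properly be entered, and exact covariates and time points are often left to an analysis plan. Every effect size above is assumed, no random-intercept case abolishes the effect, and the bias is zero when YWI acts on the score only through attention.

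Most of this stands and limits the point. It does not remove it. The article does more than leave the covariates open: it names a class of them, and two members of that class have no pre-intervention value. The conditional qualifier gives no criterion that would exclude them.

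Three stronger readings are tempting, and the document does not support them:

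- **That the primary result is biased.** It is not; these variables do not enter the GEE.
- **That the adjusted effect is certain to be biased.** The inclusion is optional, baseline distress would be legitimate, and bias needs both a link between score and outcome and a direct arm effect on the score.
- **That the plan contradicts its own intention-to-treat statement.** The conflict arises only under complete-case fitting, which the article does not state. It also concerns the chart outcome; for patient-reported attention, a woman without a survey lacks the outcome as well.

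**Conclusion.** The point holds for the follow-on GLMM and for the similar analysis of patient-reported attention. As written, the plan permits an adjusted YWI effect conditioned on outcomes measured after the intervention, and for satisfaction and quality of life no other values exist. Such an estimate can be biased when the arm also affects the score directly, which the content of the YWI materials makes plausible.

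Size and direction are unknown. Under the assumed effects, the odds ratio of 5.5 moves to between 3.7 and 6.4 in the simple logistic model, and the random-intercept model retains 80 to 100% of the log odds ratio. With no direct arm effect there is no bias. Loss of survey non-responders, at odds with the all-subjects statement, follows only if the model is fitted to complete cases. This is a correction to a supporting analysis; the primary test stands.

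**What to change.** In Planned analyses, delete the conditional clause that admits variables from the secondary analyses. State instead that the GLMM, including its use for patient-reported attention, adjusts only for pre-intervention variables: stratum, patient demographics, baseline HADS, CES-D and PSS, practice setting and pre-trial practice size.

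If the relation of attention to satisfaction, quality of life or later distress is of interest, report any model with follow-up values separately as an exploratory association or mediation analysis, and do not label it an adjusted YWI effect.

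The cost is one sentence and no new data. It should be settled before the models are run.

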## Methods

### Study design

The Young & Strong study is a multi-site, two arm, cluster randomized clinical trial with the practice site being the unit of randomization (see Figure 1). The study compares the YWI arm to a contact-time, physical activity intervention (PAI) arm. Employing a contact-time comparison intervention ensures that study results are not a function of time and attention given to patients due to their involvement in the study.

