### Overview of the interventions

There is considerable work conducted across a range of intervention topics demonstrating that patient-oriented interventions, without parallel provider or systems-level interventions, are neither well-implemented nor sustained [27-29]. Thus, we designed a multi-pronged intervention, with both provider and patient intervention components.

The YWI focuses on issues important to young women newly diagnosed with breast cancer, including fertility and early menopause, pregnancy after breast cancer, psychosocial concerns (e.g., coping with anxiety, dating, career and education issues, and dealing with young children), genetic issues, body image, and sexual functioning. The physical activity intervention (PAI), developed for this study, is a contact-time comparison intervention designed to promote physical activity. Physical activity was selected as the focus of the contact-time comparison intervention due to the known benefits of physical activity for people with cancer, not unique to young women, including: improved cardiovascular fitness, quality of life, and self-esteem [30]; reduced depression, anxiety, and tiredness; and potential lower risk of recurrence and longer survival [31].

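### The stated analysis of distress and quality of life gives one proportion per arm, although the question asked is a difference between arms

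*Protocol article*

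**What the plan says.** Three places in the protocol article set the question as a comparison of arms.

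- Abstract, Methods/Design: "Secondary outcomes include differences in patient satisfaction with care and psychosocial distress between the two study arms".
- Background, last paragraph: "Secondary aims include exploring how YWI affects attention to other issues important to young women with breast cancer". The list that follows includes satisfaction, distress and quality of life.
- Planned analyses, second paragraph: the purpose is "examining the effect of the YWI on patients’ emotional health, distress, and quality of life".

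The method then given for that purpose is "we will estimate proportions within each arm for each measure and report 95% confidence intervals". No contrast, test or model follows for these outcomes.

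The rest of Planned analyses is more specific. The primary outcome gets GEE "to evaluate binomial proportions with clustered binary data", with terms for arm and stratum and a population-averaged contrast. A mixed model with practice as a random effect follows. These methods are extended to attention to fertility as patients report it, and to no other outcome. Exercise gets a two-sample test of change from baseline, adjusted for within-practice correlation.

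Table 1 lists HADS, CES-D and PSS at baseline, 3 and 12 months, CARES-SF at 3 and 12 months, and PSQ-18 at 3 months only. The section on anxiety, depression and distress gives a cut-off for HADS (11 or more) and for CES-D (above 16). The article gives none for PSS or CARES-SF.

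**The concern.** A proportion with its interval in each arm describes two groups. It does not estimate the effect of one intervention against the other, which is what the aim and the named outcome ask for. The article does state a method here, so this is not a detail left to a later document: the stated method does not answer the stated question.

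Three weaknesses come with it. For PSS and CARES-SF it is not said what the proportion is a proportion of. Baseline HADS, CES-D and PSS are collected but not used, although the article keeps CES-D and PSS because they respond better to change than HADS. And in a "cluster randomized clinical trial with the practice site being the unit of randomization", the intervals are described without mention of practice.

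At stake is the trial's secondary evidence on distress. Followed literally, the report would hold no effect estimate for it. The choice of contrast, scale and covariates would stay open until the data are in.

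**Working it through.** **The plan's own figures.** The article states no figure for this analysis. The nearest one is the minimum sample in Statistical design: per arm 7 × 15 + 20 × 5 = 205, so 410 in all, as stated. The 80% power there concerns attention to fertility and does not bear on this point.

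**Question against method.**

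| Outcome | Between-arm contrast stated | Clustering stated | Baseline used |
|---|---|---|---|
| Attention to fertility (records) | yes | yes | not applicable |
| Attention to fertility (patients) | yes, by extension | yes, by extension | none collected |
| Exercise time | yes | yes | yes (change) |
| HADS, CES-D, PSS | no | not mentioned | no, though collected |
| CARES-SF | no | not mentioned | none collected |
| PSQ-18 | no analysis stated | no analysis stated | none collected |

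The gap lies in one sentence and does not run through the whole plan.

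**What leaving out clustering would cost.** Inputs: 105 patients per arm in sites of 15 and 100 in sites of 5 (Statistical design). The intraclass correlation (ICC) for the distress scales is not given, so 0.01 to 0.10 is assumed. A proportion of 30% is also assumed.

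- Design effect: DE = [105(1 + 14·ICC) + 100(1 + 4·ICC)] / 205.
- True coverage of an unadjusted 95% interval: 2Φ(1.96/√DE) − 1.
- Unadjusted half-width: 1.96·√(0.3 × 0.7/205) = 6.3 points. The adjusted half-width is this times √DE.

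| ICC | DE | True coverage | Adjusted half-width |
|---|---|---|---|
| 0.01 | 223.7/205 = 1.09 | 94% | 6.6 points |
| 0.05 | 298.5/205 = 1.46 | 90% | 7.6 points |
| 0.10 | 392/205 = 1.91 | 84% | 8.7 points |

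For the difference between arms, the half-width is √2 times as large: about 8.9 points unadjusted and 10.7 points at ICC 0.05.

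**What proportions without baseline cost.** For a normally distributed score (an assumption), a cut keeps the fraction φ(z)²/[q(1 − q)] of the information, where q is the share above the cut. This is 0.64 at q = 0.5 and 0.49 at q = 0.2. Adjusting for a baseline score with correlation r removes about r² of the outcome variance: 16%, 25% and 36% at assumed r of 0.4, 0.5 and 0.6. These are losses of precision, not bias.

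**The case against.** The best defence is that the secondary aims are exploratory, the sample was sized only for attention to fertility, and a condensed article may describe secondary outcomes simply. That stands as an argument about weight. It does not remove the mismatch, because exploring how an intervention affects distress still needs a between-arm estimate.

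Several stronger readings are tempting, and the article does not support them.

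- *The trial could say nothing about distress.* Two independent proportions give the point difference by subtraction, and an approximate standard error can be built from the two intervals. What is missing is a specified contrast, not the data.
- *The intervals ignore clustering.* The sentence is silent. It does not say that they are unadjusted, and the full plan may adjust them. The silence stands out because the neighbouring analyses are explicit, so the point is to make it explicit.
- *Satisfaction is cut into proportions.* The sentence covers emotional health, distress and quality of life, not PSQ-18. For satisfaction the article gives no analysis at all.
- *Quality of life is named as a between-arm outcome.* The abstract names satisfaction and distress. Quality of life enters through the secondary aims and the purpose clause in Planned analyses.
- *The baseline is wasted throughout.* This applies to HADS, CES-D and PSS only. For those, an unadjusted comparison of randomized arms is valid but less precise.
- *The comparator itself lowers distress, so within-arm figures mislead.* Overview of the interventions lists "reduced depression, anxiety, and tiredness" among the benefits of physical activity in general. It does not claim this for the study's booklet, checklists and website.

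**Conclusion.** The point holds in a limited form. For distress, the named outcome is a between-arm difference and the stated method is not. For quality of life, the same method fails the stated purpose of examining the effect of YWI. The undefined proportions and the unused baseline scores are secondary weaknesses of the same sentence. Clustering needs clarifying and is not a shown error: the 94% to 84% coverage applies only if practice is left out, and it rests on assumed ICCs of 0.01 to 0.10 and full follow-up of 205 patients per arm.

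This should be fixed, but it does not threaten the trial. It concerns exploratory secondary aims and leaves the primary analysis and its power unchanged.

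**What to change.** Replace the sentence in Planned analyses with text such as this:

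> For HADS, CES-D, PSS and CARES-SF, the YWI-minus-PAI difference in mean score at 3 and 12 months will be estimated with a 95% CI from a linear mixed model with a random practice effect, adjusted for stratum and, for HADS, CES-D and PSS, for the baseline score. Proportions above the HADS and CES-D cut-offs will be reported descriptively with cluster-adjusted CIs. These analyses are exploratory.

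Add that PSQ-18 at 3 months will be analysed with the same between-arm model without baseline adjustment, since the abstract names satisfaction and Planned analyses gives no method for it. As PSQ-18 has seven subscales, say which of them are compared.

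The cost is a change of wording and a little more programming. No new data, visits or patients are needed. If the full analysis plan already holds such a model, only the article's sentence needs to be brought into line with it.
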